#### Secondary outcomes

Liebowitz Social Anxiety Scale-Self Report (LSAS-SR): Used to measure social anxiety which is highly related to public speaking anxiety. LSAS-SR is a 48-item scale assessing anxiety and avoidance levels across 24 social situations, with the Korean version validated for university students [41]. The scale demonstrates excellent internal consistency (*α* = 0.92–0.95) [41]. LSAS-SR total scores will be summarized at the group level and compared across the same six assessment occasions used for the primary outcome (T0–T5). 

Fear of Negative Evaluation-Brief (FNE-B): A 12-item scale measuring fear of negative evaluation. Originally developed by Watson and Friend (1969) and shortened by Leary (1983) [42], the Korean version was validated by Lee and Choi (1997) [43]. Items are rated on a 5-point Likert scale, with higher scores indicating greater fear of negative evaluation [44]. FNE-B total scores will be summarized at the group level and compared across the same six assessment occasions used for the primary outcome (T0–T5). 

Physiological indicators: To objectively compare short-term anxiety induction levels and long-term desensitization patterns between groups during exposure, photoplethysmography (PPG) for heart rate measurement and galvanic skin response (GSR) measurement are implemented [45]. For cardiac autonomic activity, the principal variables will include RMSSD and SDNN (log-transformed if distributional assumptions are violated), and pNN50, derived from PPG signals collected from the earlobe at 256 Hz. For electrodermal activity, the principal variables will include mean tonic skin conductance level (SCL) and phasic SCR peak amplitude and peak count derived from GSR signals collected from the index and middle fingers of the non-dominant hand at 256 Hz. These participant-level physiological variables will be summarized by session and compared between groups across intervention stages. Signals will be processed using third-order Savitzky-Golay filters to preserve signal strength while providing smoothing [46]. Heart rate variability reflects autonomic nervous system responses to stress and anxiety [47], while galvanic skin response serves as an indicator of sympathetic nervous system arousal levels [48].

#### Exploratory variables

Behavioral indicators: Intervention effects on behaviors such as movement and vocal changes are examined in exploratory analyses. Movement is collected through fixed cameras filming participants’ upper body frontal views, with Motion Energy Analysis (MEA) used to analyze synchronization patterns with VR interviewer movements [49]. Synchronization patterns are modeled as sine wave dynamics, with amplitude and vertical offset parameters extracted as indicators of interpersonal coordination quality [49]. These synchrony metrics are correlated with session-specific anxiety levels (derived from concurrent physiological and self-report measures) and compared across sessions and participants to examine relationships between social synchrony and anxiety reduction.

Voice data from presentation speech are collected through VR microphones during sessions. Prosodic voice features such as fundamental frequency (f0), intensity contours, pause time, and speech rate will be extracted from recordings during pre-session stabilization. Speech samples will be preprocessed with noise filtering but not segmented into fine-grained phonetic units. Recordings are captured using the Meta Quest 3 headset’s built-in microphone (mono, 48 kHz). Acoustic analyses will be conducted in Praat (v6.3 or later), and all acoustic features will be standardized within participants relative to the pre-session baseline to control for inter-individual variability.

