#### First session

When the VR content begins, participants first wait in a virtual waiting area where they receive entry guidance through on-screen and audio instructions. After this brief orientation, the interviewer requests a brief self-introduction. Upon receiving the question, participants are given a 20-s preparation period (indicated by an on-screen countdown timer) to organize their thoughts before beginning their response. Participants then present for 1 min while monitoring a timer interface. In the experimental group (EG) intervention, the interviewer demonstrates positive reactions such as nodding while listening to participants’ self-introductions and responds with “Yes, I heard you well.”, “Please relax and feel free to speak comfortably.” upon presentation completion. In the control group (CG), interview questions are provided through automated voice prompts, with no visual or auditory interviewer reactions provided. Both groups participate in a 2-min “positive self-talk session” immediately following presentation simulation, after which equipment is removed and questionnaire surveys are completed. Participants are scheduled to revisit the laboratory for the second session after 48 h (± 2 h). Figure 2 shows screen captures of what participants observe through VR.

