#### Second session

Participants undergo the same stabilization session as the first session before proceeding with the interview. In the experimental group, the interviewer requests an explanation of strengths and weaknesses with a neutral expression. Participants receive a 20-s preparation period followed by 1 min for their presentation. The interviewer maintains neutral observation of the participant before examining application materials and responding “Hmm… I see” upon presentation completion. In the control group, interview questions are provided through automated voice prompts with no visual or auditory interviewer reactions. Both groups participate in a 2-min “worry reflection and acceptance practice” immediately following presentation simulation.

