#### Third session

Participants proceed with interviews following the stabilization session. In the experimental group, the interviewer displays a tired expression, sighs, makes notes on paper, and asks “Next, please tell me about the two most memorable news items you’ve seen recently and explain your reasons.” After a 20-s preparation period, participants present for 1 min. During the participant’s response, the interviewer begins whispering to another interviewer, then responds with negative expression and voice tone upon response completion: “I can’t hear your voice well, so please speak a little louder and more clearly. Also, could you explain what you mentioned in more detail?” In the control group, interview questions are provided through automated voice prompts with no visual or auditory interviewer reactions. Both groups participate in a 2-min “breathing and muscle relaxation training” immediately following presentation simulation. Across groups, the interview topics, preparation time, speaking duration, and session sequence are identical; only the interviewer reaction format differs between conditions. The positive, neutral, and negative interviewer reactions were designed as sequential components of a single graded exposure intervention rather than as separate intervention arms. Figure 3 shows the intervention process and questionnaire administration timepoints.

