Motion Energy Analysis (MEA) quantifies movement patterns using 10 frames per second video conversion and gray-scale pixel differencing methodology [49]. Motion energy vectors undergo standard smoothing and z-transformation procedures. Given that control group interviewers remain static, synchronization analysis focuses on within-experimental group patterns. Following established MEA protocols, 4-min interaction segments (question → presentation → interviewer reaction) are analyzed using 30-s sliding windows with cross-correlations computed for time-lags up to ±5 s in 0.1-s steps [49].

Voice analysis examines 1-min presentation recordings using automated prosodic feature extraction. Speech samples will be preprocessed with noise filtering but not segmented into fine-grained phonetic units, as analyses focus on suprasegmental prosodic patterns. Primary measures include fundamental frequency (F0) mean, speech rate, and pause ratio, which together reflect expressive and arousal-related vocal behavior. All features will be within-subject standardized relative to baseline readings to control for inter-individual variability. Voice features will be compared between groups and across sessions, with correlation analyses examining relationships between prosodic stress indicators (e.g., elevated F0, reduced speech rate, increased pause ratio) and concurrent anxiety measures. Expected patterns include higher F0 and slower, less fluent prosodic dynamics in early sessions, followed by progressive normalization indicating reduced performance anxiety [53].

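### The planned across-session comparison of movement synchrony with anxiety is confounded with the interviewer's script, which changes at every session in a fixed order

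*Protocol article*

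**What the plan says.** Under Exploratory variables, the protocol article films the participant's upper body and applies motion energy analysis, which is "used to analyze synchronization patterns with VR interviewer movements". Two uses of the result follow. "These synchrony metrics are correlated with session-specific anxiety levels (derived from concurrent physiological and self-report measures"), and the metrics are also "compared across sessions and participants to examine relationships between social synchrony and anxiety reduction".

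The session descriptions give the interviewer in the experimental arm a different part each time:

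- First session: "the interviewer demonstrates positive reactions such as nodding while listening".
- Second session: "The interviewer maintains neutral observation of the participant before examining application materials".
- Third session: "the interviewer displays a tired expression, sighs, makes notes on paper" around the question, and during the answer "the interviewer begins whispering to another interviewer".

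The Discussion lists the fixed positive, neutral, negative order as a limitation. Data preparation and planned analyses confines synchrony to one arm: "Given that control group interviewers remain static, synchronization analysis focuses on within-experimental group patterns". The same section specifies smoothing, z-transformation, 30-s windows and lags up to ±5 s. Its fixed-sequence caveat, which bars causal reading of the separate reaction stages, is written for the GSR analyses.

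**The concern.** A synchrony measure depends on both partners' movement. When the interviewer's movement changes, mean synchrony can change although participants coordinate no more and no less than before. Anxiety may also shift over the same three sessions: Data preparation and planned analyses anticipates falling autonomic reactivity in the experimental group. Two quantities that each vary by session will generally correlate over sessions whether or not they are linked within a person.

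Session number, script and interview topic change together, and there is no comparison arm for this analysis. The data alone therefore cannot say whether an across-session pattern reflects coordination or the script. The consequence would reach beyond one table, because the Discussion suggests that synchrony patterns might later guide adaptive versions of the therapy.

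**Working it through.** The plan states no figure to reproduce. The check is a reading of the sections above and an illustrative calculation.

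**Inputs.** From the protocol: 46 participants in the experimental arm (Sample size) and 3 sessions. Assumed: person variance 0.5 and residual variance 0.5 for both synchrony and anxiety (total SD 1), no relation between the two at any level, and session shifts of size k = 0.5 or 0.8 SD. Anxiety means are (0, k/2, k), or the same with the sign reversed.

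**Expected within-person correlation.** Each person's own mean is removed. The residual sum of squares per person then has expectation (3 − 1) × 0.5 = 1 for each variable. The session means add the following, for rising anxiety, whose deviations are (−k/2, 0, k/2) with sum of squares k²/2:

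1. *Synchrony high in Session 1 only, (k, 0, 0).* Deviations are (2k/3, −k/3, −k/3), with sum of squares 2k²/3. Cross-product: −k²/3 − k²/6 = −k²/2. So r ≈ −(k²/2) / √[(1 + 2k²/3)(1 + k²/2)].
   - k = 0.5: −0.125 / √(1.167 × 1.125) = −0.11.
   - k = 0.8: −0.32 / √(1.427 × 1.32) = −0.23.
2. *Session 3 intermediate, (k, 0, k/2).* Deviations are (k/2, −k/2, 0). Cross-product: −k²/4. So r ≈ −(k²/4) / (1 + k²/2).
   - k = 0.5: −0.0625 / 1.125 = −0.06.
   - k = 0.8: −0.16 / 1.32 = −0.12.
3. *High, low, high, (k, 0, k).* Deviations are (k/3, −2k/3, k/3). Cross-product: −k²/6 + k²/6 = 0. So r ≈ 0.

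If anxiety falls instead of rising, the sign of r reverses and its size does not change.

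**Simulated share of trials significant at 5%, with no true relation:**

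| Synchrony pattern | k = 0.5 | k = 0.8 |
|---|---|---|
| High in Session 1 only | 18% | about 64% |
| Session 3 intermediate | about 8% | 21% |
| High, low, high | about 5% | about 5% |
| Any pattern, centred by session | 4% to 6% | 4% to 6% |

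The rates are much the same whether anxiety rises or falls. Correlating the two between participants within a single session also rejects at about the nominal rate.

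**Second check, from movement series.** A separate simulation generated movement at 10 frames per second, with 30-s windows, ±5 s lags, smoothing and z-scored windows. Participants' coupling to the interviewer was identical in every session, and anxiety fell by session independently of synchrony. Only the scripted movement changed. With assumed relative movement of 1, 0.1 and 0.5, mean synchrony was 0.67, 0.26 and 0.46; with 1, 0.5 and 0.25 it was 0.67, 0.49 and 0.31. The correlation pooled over sessions was significant in 0% to 96% of runs across the scripts tried, and in 0% to 8% after session-centring. There were only 25 runs per script, so these percentages are rough. They do show that z-transformation does not remove the dependence on the script.

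**The case against.** The best defence is that the text does not commit to a pooled correlation. Correlating synchrony with session-specific anxiety can be done between participants within each session, where everyone faces the same script, and that analysis is sound. A session term or a surrogate baseline could also be specified in a fuller analysis plan that is not shown. This stands for the correlation. It does not rescue the across-session comparison, which the article states and ties to anxiety reduction.

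The analysis is labelled exploratory, and the Discussion already limits conclusions to the graded package as a whole. Both statements are true and keep the point small. Neither addresses a metric whose reference signal changes between sessions.

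A reader might infer that the interviewer is almost motionless in Session 2 and that the session should be excluded under the reasoning applied to the control arm. The documents do not support that. Only control interviewers are called static. The Session 2 interviewer asks a question, looks at papers and responds, and the analysed segment runs from question to reaction. Nor is a quiet Session 2 enough to create the problem, since the high, low, high pattern gave no inflation.

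A reader might also want a single inflation factor for synchrony. None can be given. The protocol's indicators are the amplitude and offset of a fitted sine wave, which neither simulation used, and the result depends on the real animations.

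**Conclusion.** The point holds as a minor one. Comparing synchrony across sessions, or correlating it with anxiety over sessions without a session term, mixes participants' behaviour with the script. Under the assumed shifts of 0.5 to 0.8 SD, the false-positive rate of the within-person correlation runs from about 5% to about 64%. Those shifts and the script patterns are assumptions, and the true size could be nil or could go in either direction. Comparisons between participants within one session are not affected. The primary PSAS analysis, the secondary outcomes and the sample size do not depend on this analysis.

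**What to change.** Under Exploratory variables and Data preparation and planned analyses:

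- State that synchrony will be related to anxiety between participants within the same session, or in a model with session as a fixed effect.
- State that differences in synchrony between sessions will be described only, and not read as evidence on anxiety reduction.
- Extend to synchrony the fixed-sequence caveat now written for the GSR stages.

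This changes wording only and needs no new data. The cost is fewer synchrony contrasts and slightly lower precision.

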#### Ethics statement

The research protocol was approved by the UNIST Institutional Review Board (UNISTIRB-25–049-A) on October 31, 2025. This study was designed according to the Declaration of Helsinki, Good Clinical Practice guidelines, and SPIRIT reporting guidelines [50]. Study interventions are considered low-intensity, low-risk interventions totaling approximately 1 h over 1 week. Participation is entirely voluntary and participants may discontinue the experiment at any time. Data are pseudonymized with participant identification numbers. Participants receive 40,000 KRW (approximately $28 USD) compensation for study participation.

Expected adverse events include cybersickness-related symptoms (e.g., nausea, dizziness, headache, and visual discomfort) and transient increases in anxiety during VR exposure. Unexpected adverse events will also be documented. Harms will be identified through both spontaneous participant report and structured post-session inquiry. All identified adverse events will be reviewed by the clinical psychologist and psychiatrist investigators and classified according to severity, expectedness, and relatedness to the intervention. Participants who discontinue the intervention because of adverse effects will, whenever feasible, still be invited to complete follow-up assessments.

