#### Follow-up with open-ended questions

Both groups complete questionnaires remotely at 6 and 12 weeks following the third intervention. Questionnaires include open-ended items allowing participants to freely provide feedback on whether they experienced actual presentation situations such as classes or interviews after the intervention and, if so, in what aspects they perceived intervention effects. Figure 4 shows intervention timepoints and data collection timepoints throughout the experimental process.

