**Fig. 4 Fig4:**
[figure not shown]
SPIRIT schedule of enrollment, interventions, and assessments throughout the study timeline. Timepoints are designated as follows: -T1 (online self-screening, in-person eligibility confirmation at the laboratory, written informed consent and randomization), T0 (baseline assessment), T1–T3 (immediate post-session assessments during the three VR intervention sessions), T4 (6-week follow-up), and T5 (12-week follow-up). The intervention phase (T1–T3) includes both experimental group (graded interviewer reactions) and control group (automated prompts) protocols. Primary outcomes (PSAS, LSAS-SR, FNE-B) are measured at all six timepoints, while physiological indicators (PPG, GSR) and behavioral measures (movement, voice data) are collected only during the intervention sessions (T1–T3). X marks indicate when each assessment or procedure is conducted

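### Structured harms inquiry is stated only for the three sessions; at 6 and 12 weeks anxiety scores are compared as group summaries, and nothing stated turns individual worsening or other late events into harms data

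*Protocol article*

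**What the plan says.** The Ethics statement gives the harms method in one sentence: "Harms will be identified through both spontaneous participant report and structured post-session inquiry". Its expected events are cybersickness symptoms and "transient increases in anxiety during VR exposure. Unexpected adverse events will also be documented". Adverse events, once identified, are reviewed by the clinical psychologist and psychiatrist investigators, who classify severity, expectedness and relatedness. Participants who stop because of adverse effects are still invited to follow-up where feasible.

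For the period after the last session, the follow-up section says "Both groups complete questionnaires remotely at 6 and 12 weeks following the third intervention". Those questionnaires contain open-ended items on "whether they experienced actual presentation situations such as classes or interviews after the intervention and, if so, in what aspects they perceived intervention effects".

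The self-report scales continue throughout. The Fig. 4 legend says "Primary outcomes (PSAS, LSAS-SR, FNE-B) are measured at all six timepoints". (The Outcome measurement section makes only PSAS primary; that difference in labelling does not affect this point.) The primary estimand is a between-group difference in mean PSAS change. LSAS-SR and FNE-B totals are to be summarised and compared at group level.

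In Session 3 the interviewer in the experimental arm whispers to a colleague, "then responds with negative expression and voice tone upon response completion". The control arm receives no interviewer reactions in any session.

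**The concern.** The harms sentence names two sources, and the structured one is tied to sessions. After Session 3 the stated method therefore leaves spontaneous report as the only dedicated harms source for 12 weeks. Session 3 is also where the experimental arm alone meets the negative end of the graded sequence. If that exposure left some students worse, the effect would be specific to one arm and would most naturally show after the session.

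At stake is the safety statement in the final report. The article describes the intervention as low-risk. A harms table built on the stated method would rest on solicited information for about the first week and on volunteered information after that. A reader of the results could not tell an absence of late harms from an absence of questions about them.

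**Working it through.** The plan gives no harms figure to reproduce. Its only computed figure is the sample size (78, raised to 92 for 15% attrition). It reproduces and enters here only as a denominator. The rest is a comparison of what the sections say.

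**1. Occasions with structured harms inquiry.**
- Post-baseline occasions: T1 to T5, so 5 (Primary outcome section).
- Sessions: 3, ending at T3, over about 1 week (Ethics statement).
- Structured inquiry stated: 3 of 5 occasions.
- Next described contact after Session 3: T4 at 6 × 7 = 42 days, then T5 at 12 × 7 = 84 days, both remote. By contrast, after Session 1 "Participants are scheduled to revisit the laboratory for the second session" about 48 hours later.

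**2. What T4 and T5 do measure.**
- PSAS 17 items + LSAS-SR 48 items + FNE-B 12 items = 77 structured items in both arms.
- LSAS-SR rates avoidance as well as anxiety across 24 situations.
- These scales do not depend on the answer to the open-ended items. Worsening of public speaking anxiety, social anxiety, avoidance or fear of negative evaluation is therefore recorded for every respondent.

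**3. How those scores are used.**
- PSAS enters as a difference in mean change; LSAS-SR and FNE-B as group-level summaries.
- If one participant worsens by d points, the arm mean moves by d/n. With n = 46 this is d/46 ≈ 0.022d. With n = 78/2 = 39 after the planned attrition it is d/39 ≈ 0.026d.
- A few individual deteriorations can thus sit inside an arm whose mean improves.
- Clinician review applies to identified adverse events. No sentence makes a rise in a T4 or T5 score such an event, or reports how many participants had one.

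**4. Events outside the scales.**
- Persistent dizziness or headache, low mood and seeking treatment are not what the three scales are described as measuring. The PHQ-9 item on suicidal ideation is mentioned only at screening.
- After T3 the stated sources for such events are spontaneous report and the open-ended items.
- The effects part of those items follows an if-so condition on having met a real presentation. A student who had none, by chance or by avoidance, is not clearly asked it.

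**The case against.** The strongest reply is that follow-up is far from blind to worsening. A reader might infer from the harms sentence that deterioration after Session 3 is caught only by spontaneous report, or that avoidance is never asked about. The document does not support either: all three scales are completed at T4 and T5, LSAS-SR covers avoidance, and the primary outcome itself is PSAS change through T5. A reader might also infer that the open-ended items cannot reveal worsening. That too goes beyond the text, since they invite free feedback, no skip rule is stated, and a negative answer is possible. Calling Session 3 the most adverse exposure is an inference from the positive-to-negative grading and concerns the experimental arm only.

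It is also fair to say that this is a condensed article, that a follow-up adverse-event form may exist in the full protocol, and that the harms paragraph is otherwise sound for a brief intervention: solicited and spontaneous sources, expected and unexpected events, and clinician classification.

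All of this stands, and it narrows the point. It does not remove it. The article is not silent on the method; it names the structured source and ties it to sessions. Measuring a score is also different from ascertaining a harm when the score is planned only as a group summary and has no stated route to the harms review. If a follow-up form exists, the sponsor need only say so.

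**Conclusion.** The point holds in this limited form. As stated, structured harms inquiry covers 3 of 5 post-baseline occasions and ends about one week in, while follow-up runs to 84 days after Session 3. Anxiety and avoidance are measured at T4 and T5, but individual worsening is neither counted as a harm nor linked to the clinician review. Late events outside the scales depend on volunteered or conditional answers.

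No late event rate can be derived from the document, so the number of events that might be missed is unknown and none is asserted. The conclusion assumes that the article's harms sentence is complete and that no separate follow-up adverse-event form exists. The consequence is confined to the safety conclusion; the primary efficacy comparison is unaffected. This is a worthwhile and inexpensive improvement to the stated method.

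**What to change.** 1. Extend the structured harms inquiry to the existing T4 and T5 remote questionnaires and say so in the Ethics statement. Events identified there would then fall under the classification already described.
2. Put the T4/T5 experience item to everyone in neutral wording: better, worse or unchanged, and presentations avoided as well as attended.
3. Report harms by arm over T1 to T5. Include the number per arm whose PSAS at T4 or T5 is above baseline, with the number assessed as denominator. Compare the arms and do not read either count alone, because some increases are measurement noise.

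The cost is about 1 to 2 minutes per contact, some non-specific symptom reports and one table, with no new visits or staff. Timing matters for the first two items. If recruitment closed on 31 December 2025 as planned and the last participant finished about a week later, the last T5 contact fell about 84 days after that, near 1 April 2026. If those contacts have passed, the PSAS counts by arm still need no new data, and the report should state that structured harms inquiry ended with Session 3.
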